**Trial registration number:**

NCT06886841.

STRENGTHS AND LIMITATIONS OF THIS STUDYThis is the first national prospective cohort in Switzerland to assess the health and well-being of both mothers and co-parents during the first year post partum, with national representativeness supported by a multistep weighting procedure to account for non-participation and attrition.The study combines clinical data, multilingual patient-reported outcomes, linkage to national hospital administrative databases, and institutional-level survey data from maternity units, enabling multilevel analyses of physical, mental, sexual and social health, care practices and overall well-being.The study takes a comprehensive approach by examining both adverse health outcomes and positive indicators such as well-being, parental bonding, flourishing and life satisfaction.As with most observational longitudinal studies, reliance on self-reported measures may introduce recall or reporting bias, and loss to follow-up may limit data completeness.

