Within this multidimensional approach, mental health constitutes a central component of postpartum health. It represents a major clinical and public health concern, with potential consequences for parents, infants and family functioning.^9 10^ Depression and anxiety affect a substantial proportion of mothers and co-parents,^9^,^11^ and some develop childbirth-related post-traumatic stress disorder (CB-PTSD), a subtype of PTSD with specific perinatal triggers.^12^,^14^ In Switzerland, a monocentric study with a small convenience sample reported that 20.7% of mothers and 7.2% of fathers met criteria for probable PTSD 1 month post partum.^15^ Although the study relied on a general PTSD screening tool and was affected by selection bias, it highlighted the potential magnitude of trauma symptoms and the clinical relevance of avoidance behaviours. Yet, long-term support remains limited, and trajectories of recovery are rarely monitored, despite their known consequences on quality of life.^3 16^ Avoidance and disengagement from care, recognised as key features of CB-PTSD, may also compromise help-seeking and widen existing gaps in support.

The quality and experience of care during childbirth and the postpartum period represent another key component of this framework, as they may shape health trajectories across multiple domains.^7 17^ According to the WHO, high-quality maternity care should be safe, effective, timely, equitable and people-centred and should integrate both provision and experience of care.^7 8^ Clinical practices during childbirth, such as labour induction, episiotomy, caesarean delivery or limited access to pain relief, have been associated with trauma, dissatisfaction and poor mental health outcomes.^18^ In Switzerland, postpartum follow-up includes an average of 7.9 home visits per mother, one of the highest rates in Europe.^19^ However, little is known about how the content and perceived quality of this care relate to health trajectories after childbirth. Despite growing attention to respectful maternity care, few population-based studies investigate how care provision and care experiences relate to long-term postpartum recovery, particularly in interaction with mental health, physical recovery and broader social determinants.^2 17^

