### Recruitment and participation

Recruitment was conducted across 81 maternity units and birth centres, covering all linguistic regions and representing 72% of the 112 Swiss birth facilities. All centres recruited for a total of 6 weeks, with most conducting recruitment between 17 March and 27 April 2025. In some centres, recruitment periods were staggered due to local organisational constraints; however, all recruitment activities were completed by 11 June 2025. In each centre, a local investigator coordinated recruitment and data collection. All women giving birth during the recruitment period were systematically screened for eligibility. Eligible women received oral and written information after childbirth and were invited to provide electronic informed consent for (1) extraction of clinical data from medical records and completion of online questionnaires (with the option to consent to clinical data extraction only), (2) data linkage with hospital discharge records and (3) optional recontact after the first year for future research participation. Eligible co-parents were invited following the same procedures, except that consent for access to medical data and data linkage was not required.

Among 6680 women giving birth over the study period, 6609/6680 (98.9%) mothers were screened, and 5962/6609 (90.2%) were eligible (figure 2). The most common reason for ineligibility was language barriers (n=586/647; 90.6%). A total of 5488 mothers were informed about the study, 2835/5488 (51.7%) provided consent for extraction of clinical data, and 2785/5488 (50.7%) consented to complete the questionnaires. Of those, 2337/2785 (83.9%) started the baseline questionnaire, and 2122/2785 (76.2%) fully completed it. In parallel, 3863 co-parents were screened, 3792/3863 (98.2%) were eligible, 3206/3792 (84.5%) were informed, and 1321/3206 (41.2%) provided consent. Overall, 974/1321 co-parents (73.7%) started the baseline questionnaire, and 925/1321 (70.0%) fully completed it.

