### Data collection

Data are collected from four complementary sources: (1) obstetric and neonatal clinical data from medical records, (2) self-administered online parental questionnaires, (3) a structured institutional survey completed by participating centres and (4) linkage with national hospital discharge datasets (Medical Statistics of Swiss Hospitals, which also include data from birth centres). Clinical data are recorded at baseline and include maternal medical and obstetrical history, pregnancy characteristics and complications, labour and childbirth management (eg, induction, analgesia, mode of childbirth), postpartum complications (eg, haemorrhage, infection), and neonatal outcomes such as Apgar score, birth weight and neonatal unit admission. Participants are invited to complete four online questionnaires, shortly after birth (baseline), and at 2, 6 and 12 months post partum. All questionnaires are provided in French, German, Italian and English. In parallel, a methodological collaboration was established with the Swiss-Peristat project (SNSF 222882), which aims to validate national perinatal care quality indicators. A subset of clinical data collected in SOCRATES will be used to estimate the accuracy of routinely collected hospital administrative data from the Swiss Federal Statistical Office.

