### Statistical analysis and weighing procedure

Descriptive analyses will be conducted to summarise participants’ characteristics and outcomes. Associations between predictors and outcomes will be examined using multivariable regression models, accounting for potential confounders identified through literature review, clinical expertise and directed acyclic graphs. Sensitivity analyses will be performed to evaluate the robustness of the findings. Missing items will be imputed using standard procedures whenever relevant (eg, multivariate imputation by chained equations). All analyses will be carried out using statistical software such as R or Stata.

To ensure representativeness at the national level, we will apply a weighting procedure that includes the following steps. First, base design weights are computed to account for differences in participation across maternity care institutions. Second, raking is applied to align the weighted sample distribution with known population margins, using key sociodemographic variables (education, income, age, Swiss nationality and parity). Predictive models (eg, Random Forest, XGBoost, Support Vector Machines) are employed to impute missing values in these key variables before calibration. Third, non-response adjustment weights are estimated through logistic regression using region, parental origin, education, ethnicity, age, living conditions, institution type and number of pregnancies as predictors. Predicted response probabilities from this model are then used to construct inverse probability weights, such that respondents with a lower predicted probability of response receive larger weights. To prevent undue influence of extreme weights, trimming is applied at predefined thresholds. The final adjusted weights are then assigned to all observations for subsequent analyses.

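### Neither the raking margins nor the response model includes mode of birth, so selection by mode of birth would stay in the weighted CB-PTSD prevalence

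*Protocol article*

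**What the plan says.** The section Statistical analysis and weighing procedure sets out three steps, followed by trimming.

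- Step 1: "base design weights are computed to account for differences in participation across maternity care institutions". No variables are named.
- Step 2: raking to population margins, "using key sociodemographic variables (education, income, age, Swiss nationality and parity").
- Step 3: inverse-probability weights from a logistic response model, "using region, parental origin, education, ethnicity, age, living conditions, institution type and number of pregnancies as predictors".

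The lists in steps 2 and 3 are closed. The same paragraph marks its imputation methods as examples, but not these variables. The strengths and limitations box claims "national representativeness supported by a multistep weighting procedure to account for non-participation and attrition".

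On the link with the outcome, the Introduction says that practices such as "labour induction, episiotomy, caesarean delivery or limited access to pain relief, have been associated with trauma, dissatisfaction and poor mental health outcomes". On participation, Recruitment and participation reports that women were informed and asked for consent after childbirth, that "2835/5488 (51.7%) provided consent for extraction of clinical data", and that 2785 of the same 5488 agreed to questionnaires. Data collection lists mode of childbirth among the items taken from medical records.

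**The concern.** A weighting variable earns its place when it is related both to the outcome and to taking part. The article itself documents the first relation for mode of birth. The second is plausible, because the invitation came shortly after the event that the primary outcome concerns. The article gives no data on it.

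The listed variables are sociodemographic, geographic or institutional, plus parity and number of pregnancies. Balancing them balances mode of birth only as far as they predict it. Step 1 acts between institutions, so it cannot correct selective consent by mode of birth within one institution.

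What is at stake is the primary estimate. An uncorrected imbalance shifts the prevalence without widening its interval, in a study that presents its weights as supporting national representativeness.

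**Working it through.** **Reproducing the article's figures**

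- Consent to clinical data: 2835/5488 = 51.66%, printed as 51.7%.
- Consent to questionnaires: 2785/5488 = 50.75%, printed as 50.7%. Not consenting: 5488 − 2785 = 2703, or 49.3%.
- Planned precision at 5% prevalence and 1900 responses: 1.96 × √(0.05 × 0.95/1900) = 1.96 × 0.005 = 0.0098. This agrees with the stated ±1 point.

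**Size of the bias if mode of birth is not balanced**

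Let π be the share of operative or complicated births in the population, s the share among participants after weighting, and p1 and p0 the CB-PTSD prevalence in those and in other births. Then

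bias = (s − π) × (p1 − p0).

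Assumed, because the documents give none of these: π = 0.30 and p1 = 9%. An overall prevalence of 5% (the article's planning value) gives p0 = (0.05 − 0.30 × 0.09)/0.70 = 3.29%. Overall consent is taken as 51.7%. With consent c1 among operative births, s = 0.30 × c1/0.517.

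| c1 (assumed) | implied consent, other births | s | prevalence obtained | bias (points) |
|---|---|---|---|---|
| 45% | (0.517 − 0.135)/0.70 = 54.6% | 0.261 | 0.261 × 9% + 0.739 × 3.29% = 4.78% | −0.22 |
| 40% | (0.517 − 0.120)/0.70 = 56.7% | 0.232 | 0.232 × 9% + 0.768 × 3.29% = 4.61% | −0.39 |

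These are 22% and 39% of the ±1 point margin. The sign reverses if mothers with operative births consent more often: c1 = 58.4% gives s = 0.339 and a bias of +0.22.

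The table gives no credit to the variables already listed. If they removed half of the imbalance, the errors would be 0.11 and 0.20 points.

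A second assumed grid takes π at 30–35%, s at 25–40%, and prevalence of 8% against 4% or 10% against 3%. It gives errors from 0 to ±0.7 points; the extreme is (0.25 − 0.35) × (10% − 3%) = −0.7.

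**Whether step 3 could use mode of birth**

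Consent to clinical data could be given without consent to questionnaires: 2835 − 2785 = 50 mothers. A further 2785 − 2122 = 663 agreed to questionnaires but did not fully complete the baseline one. Mode of birth comes from the medical record, so it should be known for both groups. It is therefore a usable predictor of later response.

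**Price in precision**

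Take mode of birth as the only weighting factor. The variance inflation from raking on it is π²/s + (1 − π)²/(1 − s).

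- s = 0.261: 0.09/0.261 + 0.49/0.739 = 1.008.
- s = 0.232: 0.09/0.232 + 0.49/0.768 = 1.026.

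In the second case the half-width goes from 0.98 to 0.98 × √1.026 = 0.99 points, while a bias of 0.39 points is removed.

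**The case against.** Choosing calibration variables is a judgement, and adding one improves the plan rather than correcting a contradiction. Nothing in the article shows that consent differed by mode of birth. The magnitude rests on assumed values, falls inside the planned margin, and ignores what age and parity already absorb. Mode of birth is only a proxy for how the birth was experienced, so selection within a mode would remain. The article also promises sensitivity analyses. All of this stands, and it limits the size and certainty of the point. It does not give a reason to leave out a variable that the article ties to the outcome and already collects.

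The proposed source deserves caution too. Data collection says that the national dataset is the "Medical Statistics of Swiss Hospitals, which also include data from birth centres", and objective 7 names frequency, timing and diagnosis codes. Neither says that a national table by mode of birth is available. The same section describes a project that uses the cohort's clinical data to check the accuracy of routine hospital data. That makes corresponding perinatal items likely, but it also means that their quality is still being assessed.

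Three stronger readings are tempting and are not supported:

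- A reader might infer that region and institution type are uncorrected. Both are predictors in step 3, and step 1 addresses institution participation.
- A reader might infer that the facilities that did not recruit (112 − 81 = 31) are ignored. Step 1 may cover them, and an article can leave that detail to the full plan.
- A reader might infer that raking is the only correction for refusal at consent. The article does not say what the screening records hold for women who declined, nor whether step 3 models refusal, later non-response or both.

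**Conclusion.** The point holds for mode of birth. The raking margins and the response predictors are fixed, and neither includes a birth characteristic beyond parity or number of pregnancies. The article reports that birth interventions are associated with trauma, and about half of the informed mothers did not consent to questionnaires. If consent or response depends on mode of birth, the weighted CB-PTSD prevalence keeps the part of that bias that the listed variables do not explain.

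On the main assumed values this is about 0.2 to 0.4 points before any credit for the listed variables. The direction is unknown, and the true value could be zero. The conclusion rests on two assumptions: that prevalence differs by mode of birth, for which the article reports an association without figures, and that participation differs by it, which is plausible but undocumented.

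**What to change.** 1. Add mode of birth, collapsed to a few categories, to the raking margins in step 2. Use aggregate national hospital statistics for the nearest available period. First confirm that the source supplies this margin and that it covers the births the cohort is meant to represent.
2. Add mode of birth to the step 3 response model. It is extracted for mothers who consented to clinical data, whether or not they answered later questionnaires.
3. If the national margin turns out to be unavailable, keep item 2 and state that selection by mode of birth at consent is not calibrated.

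The change affects only the weighting, so data collection is untouched. It costs one aggregate data request, some code and slightly more variable weights. In the illustration the variance rises by 0.8% to 2.6% for this factor alone. That loss should be watched, since 2122 mothers fully completed baseline and the precision target needs 1900 responses at 2 months. Collapsing categories and the planned trimming keep it small.

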**Methods and analysis:**

SOCRATES is a prospective, population-based cohort study conducted in all linguistic regions of Switzerland. Eligible participants include women aged 14 and above who gave birth to a live or stillborn infant (≥22^+0^ weeks’ gestation and ≥500 g) and their cohabiting co-parents, provided they speak German, French, Italian or English. Recruitment was conducted in 81 of the 112 Swiss maternity units, birth centres and organisations of midwives over 6 weeks in spring 2025. Clinical data on pregnancy, childbirth and the early postpartum period are extracted from medical records. Postpartum hospitalisation data are obtained through linkage with national medico-administrative databases. Participants complete online questionnaires shortly after birth and at 2, 6 and 12 months post partum, including sociodemographic characteristics and patient-reported outcomes. The primary outcome is the prevalence of childbirth-related post-traumatic stress disorder at 2 months, assessed using the City Birth Trauma Scale. Secondary outcomes include depression, physical recovery, sexual health, quality of life, healthcare use, perceived care quality and overall well-being. A weighting procedure will be used to ensure representativeness and to account for attrition.

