### Sample size and power calculation

The required sample size was determined a priori based on the primary objective of estimating the prevalence of CB-PTSD in mothers at 2 months post partum. Assuming a prevalence of 5% in high-income countries^21^ and aiming for a 95% CI with a ±1% margin of error, we estimated that at least 1900 complete responses at 2 months would be needed. Anticipating a 60% follow-up rate, based on previous large-scale perinatal cohorts,^22 23^ we set a baseline recruitment target of approximately 3200 women. This sample size also allows for planned subgroup analyses on care practices.^24^

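### The non-response weights leave out baseline psychological scores and birth data that the study already collects, so dropout related to CB-PTSD is only partly corrected

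*Protocol article*

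**What the plan says.** The Abstract (Methods and analysis) defines the target: "The primary outcome is the prevalence of childbirth-related post-traumatic stress disorder at 2 months, assessed using the City Birth Trauma Scale". The same paragraph says the weighting is meant to secure representativeness and deal with attrition. The strengths and limitations box repeats this for both non-participation and attrition.

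The section Statistical analysis and weighing procedure sets out three steps:

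1. Design weights for differing participation across institutions.
2. Raking to population margins on education, income, age, Swiss nationality and parity, with missing values in these variables imputed by predictive models.
3. A logistic response model "using region, parental origin, education, ethnicity, age, living conditions, institution type and number of pregnancies as predictors", inverted to give weights, which are then trimmed.

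The step-3 list has no 'eg', although the same section uses that qualifier for its imputation method and its predictive models. It does not say which response step 3 models: participation, start of the baseline questionnaire, or return at 2 months. Other provisions are general: unspecified sensitivity analyses and imputation of missing items.

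On available data, Data collection states: "Clinical data are recorded at baseline and include maternal medical and obstetrical history, pregnancy characteristics and complications". It goes on to list induction, mode of birth, haemorrhage and neonatal unit admission. Table 1 shows EPDS/EPDS-3A, PDEQ, QACE and PSS-4 at childbirth for both parents.

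**The concern.** Inverse-probability weights remove attrition bias only with respect to what is in the response model. The eight listed predictors are sociodemographic, geographic or institutional, plus number of pregnancies. None describes how this birth went or how the parent was doing shortly afterwards.

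The Introduction gives a reason to expect those features to matter: "Avoidance and disengagement from care, recognised as key features of CB-PTSD, may also compromise help-seeking". It also links induction, episiotomy, caesarean delivery and limited pain relief to trauma. If response at 2 months depends on early distress or on the birth, and these also predict CB-PTSD, weighted prevalence will still differ from true prevalence. The report would nevertheless describe attrition as accounted for.

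A second loss comes earlier. Recruitment and participation reports, for consenting mothers, that "2337/2785 (83.9%) started the baseline questionnaire, and 2122/2785 (76.2%) fully completed it". Some of the listed predictors seem to come from the very questionnaire that these women did not open.

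**Working it through.** **1. The plan's own figures.** Sample size and power calculation assumes 5% prevalence and a 95% CI of ±1 point.

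- n = z²p(1−p)/d². With z = 1.96: 3.8416 × 0.05 × 0.95 / 0.0001 ≈ 1825. With z = 2: 4 × 0.0475 / 0.0001 = 1900, the stated figure.
- 1900 / 0.60 = 3167, consistent with the target of about 3200.

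The yardstick is therefore 1 percentage point, with 40% loss expected.

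**2. Bias if a distress-related factor is left out.** The documents give no response rates by distress, birth experience or CB-PTSD status, so these inputs are assumed. A fifth of mothers have high baseline distress or dissociation. CB-PTSD is 15% in them and 2.5% in the rest, so overall 0.2 × 0.15 + 0.8 × 0.025 = 5%. Overall response is 60%, and the listed predictors are taken to capture none of the difference.

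With r_H the response in the high group, r_L = (0.60 − 0.2 r_H)/0.8 and observed prevalence = (0.2 × r_H × 0.15 + 0.8 × r_L × 0.025)/0.60.

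| r_H | r_L | Observed | Bias (points) |
|---|---|---|---|
| 50% | 62.5% | 0.0275/0.60 = 4.58% | −0.42 |
| 45% | 63.75% | 0.02625/0.60 = 4.38% | −0.62 |
| 40% | 65% | 0.0250/0.60 = 4.17% | −0.83 |

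These cases correspond to a case to non-case response ratio of about 0.91 to 0.83.

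**3. The same bias by response ratio.** If ρ is the ratio left after weighting, observed = 0.05ρ/(0.05ρ + 0.95).

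- ρ = 0.9: 0.045/0.995 = 4.52%. Nominal 95% CI coverage at n = 1900 is about 83%.
- ρ = 0.8: 0.040/0.990 = 4.04%. Coverage is about 43%.
- ρ = 1.1: 0.055/1.005 = 5.47%. The bias is the other way if affected parents respond more.

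**4. How much the listed predictors might recover.** A simulation of one million records assumed 5% prevalence, 60% response, an odds ratio of 2.5 for CB-PTSD per SD of baseline distress, a correlation of 0.2 between distress and a sociodemographic score, and response depending on both.

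| Response OR per SD of distress | Unweighted | Sociodemographic weights | Plus baseline distress |
|---|---|---|---|
| 0.85 | 4.52% | 4.71% | 4.99% |
| 0.75 | 4.34% | 4.53% | 5.01% |
| 0.65 | 4.10% | 4.27% | 4.97% |
| 0.50 | 3.80% | 3.96% | 5.03% |

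Sociodemographic weights recover between 0.16/1.20 = 13% and 0.19/0.48 = 40% of the bias, leaving −0.29 to −1.04 points. Adding baseline distress removes essentially all of it here, because dropout depends only on measured variables. When CB-PTSD itself also lowers response (OR 0.8), the fuller model still leaves about −0.4 to −0.5 points.

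**5. The never-starters.** 2785 − 2337 = 448, and 448/2785 = 16.1%. The Abstract and Outcome measures and instruments describe sociodemographic items as questionnaire content, and the clinical list in Data collection does not include them. Education is a raking variable, so the stated imputation covers it. Ethnicity and living conditions are not raking variables and are not covered. Region, age, institution type and number of pregnancies could be known from the site or the record. Consent to questionnaires came together with consent to clinical data extraction, so record data should exist for these 448 women.

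**The case against.** Several counter-arguments have force.

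- *Partial correction is real.* Dropout that runs through education, origin, living conditions, age or institution type is corrected. A reader might infer that dropout linked to CB-PTSD goes wholly uncorrected. The documents do not support that, and the table in step 2 sets this correction to zero by assumption.
- *The direction is not shown.* A reader might infer that the primary prevalence will be too low. The avoidance sentence in the Introduction concerns care and help-seeking, not answering an online questionnaire. Parents with a difficult birth might be keener to take part in a study named for traumatic birth. The sentence makes under-estimation plausible and no more.
- *The size is assumed.* The cases in step 2 rest on a sixfold risk difference (15% against 2.5%), and all stay inside the ±1-point margin.
- *The never-starters are not beyond weighting.* A reader might infer that the model cannot be used for them at all. Imputed education and predictors known from records would allow partial use.
- *Detail may sit in an analysis plan that is not shown.* That may be so for wave-specific models and named sensitivity analyses. It does not answer the point about the predictors, because the article states that list and states it as complete.

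What stands is the choice itself: a closed predictor list that passes over relevant data already in hand, beside a claim that attrition is accounted for.

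**Conclusion.** The concern holds in a limited form. The stated weights correct dropout related to CB-PTSD only so far as the listed predictors carry it. Early psychological scores and birth variables are collected in time, plausibly predict both outcome and response, and enter no weighting step.

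The size and direction of the remaining bias cannot be known from the documents. Under the assumptions in step 2 it is about 0.4 to 0.8 points, a large share of a ±1-point margin. The simulation, which allows partial correction, gives about 0.3 to 1.0 points.

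The article leaves open which response step 3 models. If it means initial participation only, loss at 2 months has no stated model. For the 16.1% who never started baseline, the listed model can be only partly applied.

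This should be fixed because it bears on the primary estimate and the remedy needs no new data. The documents do not show that the estimate is wrong.

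**What to change.** 1. State which response step 3 models.
2. From consent to baseline questionnaire, model response on medical-record variables: mode of birth, induction, haemorrhage and neonatal unit admission, with age, parity and institution.
3. From baseline to each follow-up, keep the listed predictors and add baseline EPDS/EPDS-3A, PDEQ, QACE, PSS-4 and the birth variables. Impute these for mothers who started but did not finish baseline (2337 − 2122 = 215). Multiply the two inverse probabilities.
4. For co-parents, use the corresponding baseline variables. Table 1 lists all four scales for them at childbirth.
5. Add a delta-type sensitivity analysis for dropout that depends on CB-PTSD itself, which baseline covariates cannot fully remove. For example, report q/(q + ρ(1−q)), where q is the weighted prevalence, over a stated range of ρ on both sides of 1.
6. Say that this does not address non-consent: 2785 of 5488 informed mothers (50.7%) agreed to questionnaires.

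The cost is plan wording and some extra modelling. The weights will be somewhat more variable, which the planned trimming limits. The change should be fixed before the primary outcome is analysed.
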